## Plumpy'Doz' Administration

### Dosing Procedures

For children in the SMC + LNS intervention arm, LNS will be provided to eligible children 6 to 24 months of age and is intended for daily use during the four-month intervention period. The monthly ration of LNS will be provided to the primary caregiver by the CDD at the same time of SP-AQ distribution. The first serving of LNS will be provided alongside the first dose of SP-AQ under DOT. The product does not require any preparation, and should not be cooked or diluted. Caregivers will be instructed that LNS should be given in addition to breast milk and other available foods. The LNS will not be provided to children less than 6 months of age, so as not to interfere with exclusive breastfeeding. Following the first dose, parents/guardians will be instructed to continue to serve eligible children LNS daily following the serving guidelines in Table 6. The recommended daily dose of Plumpy'DozTM is 1.5 teaspoons (6-11 months of age) or 3 teaspoons (12-23 months of age), served 3 times per day; this is a total of 23 grams per day for children 6-11 months of age and 46 grams per day for children 12-23 months of age. One container of 325 grams is intended to serve one child for one week and each child will receive 4 containers for the entire month alongside the monthly SP-AQ treatment course. The pot will need to be resealed and stored in hygienic conditions between servings.

Table 6. Recommended Daily and Monthly Dosing of Plumpy'Doz

| Age (months) | Recommended Plumpy'Doz Servings, per Day | Kilocalories, per Day | Number of Servings, per Day | Recommended Plumpy'Doz Servings, per Month |
|--------------|------------------------------------------|-----------------------|-----------------------------|--------------------------------------------|
| 6-11         | 23 grams                                 | 123 kcal              | 3 servings                  | 690 grams                                  |
| 12-23        | 46 grams                                 | 147 kcal              | 3 servings                  | 1,380 grams                                |

## 5 Monitoring and Evaluation Methods

Table 7 presents the data collection methods used for evaluation of the performance metrics previously outlined in Table 3, and the target population. Estimating intervention treatment coverage will be assessed through the midline cross-sectional household survey. The impact of interventions on nutrition health outcomes will be assessed through the three repeated cross-sectional household surveys. The impact of interventions on malaria health outcomes will be assessed through a case-control study using a malaria tracker where cases will be recruited from health facilities and control from the midline household survey. Cases will be recruited from facilities due to the challenge of identifying sufficient numbers of acute malaria episodes via monthly household surveys. Focus Group Discussions (FGDs) will be used to provide context to the results. CHAI will contract a private data collection firm to carry out the household surveys, case control study, collection of health facility records, and completion of FGDs. CHAI will carry out the data analysis and provide CIFF the full clean datasets from the firm upon request to validate findings.

Table 7: The data collection methods used for evaluation of the performance metrics previously outlined in Table 3, and the target population.

| Data Collection Method                                              | Timeline      | Inclusion Age*                | Location                     | Indicators                         |
|---------------------------------------------------------------------|---------------|-------------------------------|------------------------------|------------------------------------|
| Baseline Household Survey                                           | July 2014     | 6-24 months                   | Community                    | Malnutrition                       |
| Midline Household Survey
Nutrition Module
SMC Coverage Module | November 2014 | 6-28 months
(3-63 months)^ | Community                    | Malnutrition
Treatment Coverage |
| Endline Household Survey                                            | May 2015      | 12-34 months                  | Community                    | Malnutrition
Prevalence         |
| Malaria Case Tracker                                                | Continuous    | 6-24 months in July 2014      | Health Facility
Community | Malaria Incidence                  |
| Focus Group Discussions                                             | November 2014 | Parents/Guardians/CDDs        | Community                    | Qualitative data                   |

\*Note: Once a child is enrolled in the intervention, he/she will remain eligible even if he/she ages out during the study. Therefore, eligible age class continuously evolves.

^At midline the exclusion criteria is having a child 6-28 months of age, however, to estimate coverage among older children SMC coverage will be collected about all children 3-59 months of age living in the home.

## **Evaluation Data Collection Procedures and Participant Recruitment**

### **Household Surveys**

In total, three household surveys will be conducted, a baseline in July of 2014 alongside the first administration, midline in November 2014 after Round 4 of administration, and a final survey in May 2015, six months post intervention. The baseline survey will provide baseline information on demographics, and nutrition indicators. The midline survey will provide an estimate of the intervention coverage and adherence to SMC in addition to the nutrition indicators. The final survey six months after the endline administration will determine if there is a long-term health impact in terms of the nutrition indicators. Each questionnaire will be a pre-tested, interviewer-administered questionnaire lasting about 45-60 minutes.

For each survey, 1,500 households with at least one child that meets the inclusion age outlined in Table 6 will be selected to participate in the survey (a minimum of 750 households in each intervention study arm: SMC and SMC + LNS). This sample size is powered to measure a 10% difference in the outcome indicator (intervention coverage or nutrition indicator is estimated at 50%, which is conservative and gives the largest sample size) between the two intervention areas with an alpha of 5% and a power of 90%, and a design effect of 1.5.

A multistage stratified sampling strategy will be used for household selection. The sampling frame for the survey will come from the national sampling frame, which lists all the Enumeration Area (EA) maps of the 2006 Population and Housing Census conducted by the National Population Commission. Assuming 25 households are interviewed per EA, EAs are needed to achieve the total target sample size – in other words 30 EAs in each intervention arm. To account for the unlikely event that a randomly chosen EA did not contain 25 eligible households, 20 additional EAs will be randomly selected per intervention arm, making a total of 100 EAs selected per survey round (50 EAs per intervention arm). The supplemental EAs will only be used if needed. Using the 2013 population projections of each ward, we will use a probability-proportional-to-size methodology to select an appropriate number of EAs within each ward.

At the second stage, a systematic random sampling will be used to select 25 households per EA. The random selection of households in each EA will proceed as follows: starting from any point, the fieldworker will walk around the selected EA to identify and list all households. In listing the households, the address and the name of head of households will be recorded for only those households with at least one child that meets the inclusion age outlined in Table 7. All institutional households will be excluded. The number of eligible households in each EA will be divided by 25 to obtain the sampling interval  $k$ . A number  $j$  between 1 and  $k$  will be randomly selected using simple random sampling. The household corresponding to this number in the list of households will be the first household to be

---

 Should be possible to obtain desired sample size based on household demographic breakdown from CHAI's SMC 2013 household survey in Kano, Nigeria.

included in the sample. To determine subsequent households to be included in the sample,  $k$  will be added each time, i.e.,  $j + k$ ,  $j + 2k$ ,  $j + 3k$ , etc., and  $k$  will vary from one EA to the other depending on the number of eligible households.

Any household within the study's catchment area with at least one child that meets the inclusion age outlined in Table 7 is eligible for selection. In selected households, an enumerator will visit the home and make an accurate listing of all children that meets the inclusion age outlined in Table 6. In each selected home, after the informed consent/assent is gathered, the head of household (either male or female) will be interviewed about the household demographics and caregivers will be asked specific questions about all eligible children in their care.

Household survey inclusion criteria are that the respondent must:

- 1.) Reside in the intervention catchment area.
- 2.) Be the primary parent/guardian or parent for a child that meets the inclusion age outlined in Table 7.
- 3.) Must provide informed consent (for parents/guardians who are between the ages of 12-18 they must provide informed assent and if their parent/guardian is nearby, this parent/guardian must also provide informed consent form).

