## 4 Intervention Design

### Study Site and Population

Table 4: Overview of the study population for each treatment type.

| Intervention Arm                                               | LGA    |
|----------------------------------------------------------------|--------|
| Arm 1: SMC (Children 3-59 months)                              | Madobi |
| Arm 2: SMC (Children 3-59 months) + LNS (Children 6-24 months) | Madobi |

This study has two intervention arms: SMC delivery and SMC + LNS delivery. Of note, SMC is specified by the WHO for children 3-59 months and Plumpy'doz' is specified by UNICEF and WFP for children 6-24 months, this study will treat children in intervention arms based on these recommendations (see Table 4: Intervention Arm). In the Local Government Area (LGA), Madobi, between 1 and 3 wards were selected for each intervention arm. An overview of the study population for each intervention area is presented in Table 4. The intervention areas were chosen to be as similar as possible in terms of pre-determined criteria that included malaria incidence reported at public health centers, wasting prevalence, malaria endemicity, socio-economic status, urbanicity, mobility and cultural identity of the population, density of health facilities, presence of a CMAM facility, and population demographic structures (dependency ratio, fertility rate and household size, infant mortality, and birth spacing).

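### The stated 90% survey power holds only for a single-round comparison with no between-ward variance, yet treatment was set by one to three chosen wards per arm

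*Protocol*

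**What the plan says.** Section 5, Household Surveys, sets "a minimum of 750 households in each intervention study arm" for each of three rounds. It adds: "This sample size is powered to measure a 10% difference in the outcome indicator". The indicator "is estimated at 50%, which is conservative and gives the largest sample size", and the calculation is made "with an alpha of 5% and a power of 90%, and a design effect of 1.5". The sample is 25 households per enumeration area (EA), "in other words 30 EAs in each intervention arm".

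Section 4, Study Site and Population, says where treatment was set. Within one LGA, "between 1 and 3 wards were selected for each intervention arm". The areas were chosen to resemble each other on a list of criteria; no random allocation is described.

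Section 5 also says how the results are read. For nutrition (H-2), "The impact of interventions on nutrition health outcomes will be assessed through the three repeated cross-sectional household surveys", in July 2014, November 2014 and May 2015. Coverage and adherence (H-1) come from the midline survey alone. Q-1 and Q-2 in Table 1 both ask whether packaging LNS with SMC produces a difference.

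**The concern.** The power sentence describes two areas compared in one round, with clustering summarised by a factor of 1.5. The design departs from that in two ways.

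- **Unit of treatment.** Wards, not EAs or households, received one package or the other. With one to three chosen wards per arm, a single-round difference is the effect of adding LNS plus whatever difference the wards already had. Sampling more EAs or households in the same wards does not remove that second part.
- **Contrast for H-2.** A baseline is collected, so the pre-existing difference can be subtracted. Doing so brings in the sampling error of two more survey estimates, which the calculation does not include.

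Two errors could follow. A chance or historical ward difference could be read as an effect of LNS. A null nutrition result could be taken as conclusive because the study was said to have 90% power. The Protocol (sections 2 and 8) expects the findings to inform decisions in other States and global policy, so the general reading matters.

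**Working it through.** **Inputs from the Protocol:** 750 households per arm per round; 50% against 60%; alpha 5% (two-sided taken, sidedness not stated); design effect 1.5; 25 households per EA; one to three wards per arm. **Not given, so assumed:** the between-ward SD, and independence of the survey rounds.

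**1. The stated figure.** Effective size per arm = 750/1.5 = 500.
SE = sqrt[(0.25 + 0.24)/500] = 0.0313.
Power = Φ(0.10/0.0313 − 1.96) = Φ(1.23) = 89%.
The 90% is reproduced to within about a point.

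**2. What the 1.5 can hold.** With 25 households per EA, 1 + 24 × ICC = 1.5 gives an EA-level ICC of 0.5/24 = 0.021. The Protocol does not give the source of the 1.5. It fits ordinary EA clustering, and no separate ward term is stated.

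**3. Adding ward variation to a single round.** With w wards per arm and ward SD s, total variance = 0.0313² + 2s²/w. A test using only the 0.0313 rejects a true null with probability 2[1 − Φ(1.96 × 0.0313/total SE)]. Power with the full variance is Φ(0.10/total SE − 1.96). At s = 3 points (assumed; at 50% this is a ward ICC of 0.0009/0.25 = 0.0036):

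| Wards per arm | Total SE | False-positive rate of the nominal 5% test | Power for 10 points, full variance |
|---|---|---|---|
| 3 | 0.0397 | 12% | 71% |
| 2 | 0.0434 | 16% | 64% |
| 1 | 0.0527 | 24% | 47% |

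At s = 5 points (also assumed) the false-positive rates are 23%, 30% and 43%. At s = 0 they return to 5%, with power 89%.

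These powers treat the ward variance as known. If it is estimated from the ward means, a t test with 2w − 2 degrees of freedom has at most 67% power with three wards per arm and 42% with two, even at zero ward variance. With one ward per arm there are no degrees of freedom and the test cannot be done.

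**4. Change from baseline (H-2 only).** With independent rounds and p1 as the baseline level in both arms, unchanged in the comparison arm:
variance = [3 × p1(1 − p1) + p2(1 − p2)]/500.
At 50% against 60%: (0.75 + 0.24)/500 = 0.00198, so SE = 0.0445. Against a single-round variance of 0.49/500 = 0.00098, this is about double.
Power = Φ(0.10/0.0445 − 1.96) = Φ(0.29) = 61%.
Difference detectable with 90% power = 3.24 × 0.0445 = 14.4 points.

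| Change in the LNS arm | SE | Power |
|---|---|---|
| 50% to 60% (or to 40%) | 0.0445 | 61% |
| 40% to 30% | 0.0431 | 64% |
| 30% to 20% | 0.0397 | 71% |
| 20% to 10% | 0.0338 | 84% |
| 15% to 5% | 0.0293 | 93% |

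The table contains no ward-by-time variation; any such variation lowers every entry. Overlap of EAs between rounds with positive correlation would raise them.

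**The case against.** The best defence is that the stated power matches the stated comparison. Household Surveys speaks of a difference between the two areas, H-2 in Table 2 is worded arm against arm, and 89% is what that contrast gives. No change-from-baseline analysis is named; it is inferred from the repeated surveys. The areas were matched on wasting prevalence, malaria incidence and socio-economic status among other criteria, which may make ward differences small. If the aim were only to describe these wards, the EA-based calculation would stand.

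Much of this stands, and it rules out several stronger readings a reader might infer:

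- **That true power is simply 61%.** This holds only at 50% prevalence, which the Protocol itself calls conservative. For a 10-point fall from 15% the change contrast has 93%.
- **That the single-round calculation is wrong for H-1.** Coverage and adherence are measured at midline only, so a single round is the right contrast; only the ward point applies.
- **That the two penalties add.** The 12% to 43% false-positive rates belong to the single-round test. A change from baseline cancels stable ward differences and leaves ward-by-time variation.
- **That the planned analysis treats EAs as independently treated.** The Protocol fixes no analysis model; that may be in an SAP not shown.
- **That 750 is materially too small.** The formula gives 515 × 1.5 ≈ 772, but 750 costs about one point of power and is stated as a minimum.

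The defence does not answer Q-1 and Q-2, which ask what packaging LNS brings about. Matching is described without any size for the residual ward difference, and the power sentence carries no condition limiting it to the chosen wards.

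**Conclusion.** The concern holds in this form. The 90% (recomputed 89%) is right for a single-round comparison with no between-ward variance, and the design does not secure that condition, because one to three chosen wards per arm determine treatment. How much is lost on a single-round test depends on a ward SD the Protocol does not give; the figures at 3 and 5 points are illustrations. For H-2, the contrast that removes stable ward differences has about twice the sampling variance if rounds are independent. At design effect 1.5 its power for 10 points is 61% at the Protocol's planning value and passes 90% only at low prevalence, before any ward-by-time variation. The correction is worth making because it is cheap and the findings are meant to travel beyond these wards.

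**What to change.** 1. Name the H-2 estimate as the between-arm change from baseline (arm by round), with standard errors clustered at least by EA.
2. Restate power for that contrast as conditional on the selected wards, assuming independent rounds and design effect 1.5: about 61% for 10 points at 50% (90% power needs about 14 points), 71% for 30% to 20%, 84% for 20% to 10%, and lower with any ward-by-time variation.
3. State that the 90% figure (about 89%) applies to H-1 only as a comparison of the selected wards.
4. State that p-values computed this way leave out between-ward variation for H-1 and ward-by-time variation for H-2, and limit conclusions about packaging LNS in general accordingly. EA clustering does not supply either component.

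**Cost:** wording only; no extra households or wards. The downside is wider H-2 intervals and a less favourable stated power.

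### The household survey takes its age rule from Table 6, the LNS dosing table, instead of Table 7; followed literally, it excludes every child aged 24 months or more, roughly half at endline

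*Protocol*

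**What the plan says.** Two sentences under Household Surveys (section 5) send the reader to Table 6 for the age rule.

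- Sample-size paragraph: "1,500 households with at least one child that meets the inclusion age outlined in Table 6 will be selected to participate in the survey".
- Listing of children in selected homes: "an enumerator will visit the home and make an accurate listing of all children that meets the inclusion age outlined in Table 6".

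Table 6 is in section 4, under Plumpy'Doz' Administration, and is titled "Table 6. Recommended Daily and Monthly Dosing of Plumpy'Doz". Its two age rows follow the text above it: "23 grams per day for children 6-11 months of age and 46 grams per day for children 12-23 months of age".

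The same Household Surveys text cites Table 7 three times. Addresses are recorded for "only those households with at least one child that meets the inclusion age outlined in Table 7". The sentence just before the child-listing rule reads "Any household within the study's catchment area with at least one child that meets the inclusion age outlined in Table 7 is eligible for selection". The second respondent criterion also uses Table 7.

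Table 7 has an inclusion-age column: 6-24 months in July 2014, 6-28 months in November 2014 and 12-34 months in May 2015. Its note says that enrolled children stay eligible as they age, so the age class moves. The indicator definitions in Table 3 carry a similar note.

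The second footnote to Table 7 says "At midline the exclusion criteria is having a child 6-28 months of age", and that "SMC coverage will be collected about all children 3-59 months of age living in the home". The midline row itself gives 3-63 months for that module.

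**The concern.** The two Table 6 sentences decide which households count towards the 1,500 and which children are listed in them. They therefore fix who enters the coverage and nutrition percentages. Table 6 has an age column, so the wrong reference does not fail visibly: it gives a usable rule, 6-23 months at every survey. That rule contradicts the Table 7 references around it and the principle that the window follows the cohort.

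Most is at stake at endline. It is the only survey meant to show whether a nutrition effect lasts, and by then much of the cohort has passed 23 months. Fieldwork is contracted to an outside firm, so the written rule needs to be unambiguous.

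**Working it through.** **Inputs.** Table 6 ages: 6-23 months. Table 7 windows: 6-24, 6-28 and 12-34 months. Survey dates: July 2014, November 2014 (+4 months) and May 2015 (+10 months). LNS eligibility (section 4): 6-24 months at round 1, plus children who reach 6 months before round 2, 3 or 4, the last in October. The protocol gives no age distribution, so ages are assumed uniform by completed month.

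**Step 1: reproduce Table 7.** The upper limits are the July limit carried forward: 24 + 0 = 24, 24 + 4 = 28, 24 + 10 = 34. The endline window is the midline window moved on six months: 6 + 6 = 12 and 28 + 6 = 34. So Table 7 follows the cohort and Table 6 does not.

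**Step 2: bands lost under 6-23 months.** Share lost = (bands of 24 months or more) / (all bands in the group).

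| Survey | Group | Ages at survey | Lost / total | Share |
|---|---|---|---|---|
| Baseline | Table 7 window (same as July cohort) | 6-24 | 1/19 | 5% |
| Midline | Table 7 window | 6-28 | 5/23 | 22% |
| Midline | July cohort | 10-28 | 5/19 | 26% |
| Endline | Table 7 window | 12-34 | 11/23 | 48% |
| Endline | All ever LNS-eligible | 13-34 | 11/22 | 50% |
| Endline | July cohort | 16-34 | 11/19 | 58% |

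The ever-eligible group starts at 13 months because a child aged 3 months in July turns 6 months by October and is 3 + 10 = 13 months old in May.

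If the July upper limit means exactly 24.0 months, the endline shares are 10/22 = 45%, 10/21 = 48% and 10/18 = 56%. The endline range is therefore 45-58%. On that exact reading the earlier losses are also smaller: none at baseline, and 4/22 = 18% to 4/18 = 22% at midline.

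**Step 3: bands admitted at endline under 6-23 months.** There are 18 bands.

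- 16-23 months: 8 bands, in the July cohort.
- 13-15 months: 3 bands, aged 3-5 months in July, who could age in to LNS.
- 6-12 months: 7 bands, under 3 months old or unborn in July, never LNS-eligible.

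The check is 8 + 3 + 7 = 18, and the never-eligible share is 7/18 = 39%. Under Table 7 only the 12-month band is of this kind, 1 of 23.

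**Step 4: the footnote.** Children aged 3-59 months in July are 3 + 4 = 7 to 59 + 4 = 63 months old in November. A limit of 59 months leaves out ages 60-63, which is 4 of the 57 July bands (7%). The SP-AQ inclusion criteria keep children enrolled after they turn 60 months.

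**The case against.** The best defence is that no careful reader would be misled. Table 6 has no inclusion-age column and Table 7 has one. Table 7 is cited three times nearby, once in the sentence just before the faulty one, and the notes say that the age class evolves. Table numbering slips elsewhere too: the adverse-reaction procedure is a second Table 5. This stands as far as intent goes. The slip is editorial and nobody chose to restrict the ages. It does not make the written rule correct.

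Three stronger readings are tempting, and the documents do not support them.

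- *Most of the treated cohort is lost at endline.* This is true only of children aged 6-24 months at round 1 (56-58%). Counting children who aged in, or using Table 7's own window, the loss is half or slightly less.
- *The endline would measure mostly the wrong children.* Seven of 18 admitted bands were never LNS-eligible, which is not a majority. If households are chosen by Table 7, younger children enter only where a child of 12-34 months also lives, so the share could be lower.
- *The sample shrinks and power falls.* The sample-size paragraph applies Table 6 to the households as well, so on that reading all 750 per arm hold a Table 6 child. A shortfall appears only if that sentence is ignored, the child-listing sentence is obeyed and each household has one eligible child. The survey asks about all eligible children. No power figure can be claimed.

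The footnote slips are also limited. The 3-59 versus 3-63 conflict concerns SMC coverage among older children and not the H-1 and H-2 percentages, which are defined on the evolving 6-24-month class. Calling the midline age rule an exclusion is a plain wording error beside an inclusion-age entry of 6-28 months.

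**Conclusion.** The point holds as a cross-reference error in an operative selection rule, found in two places and contradicted by the surrounding text. Read literally, it excludes all children aged 24 months or more: about 5% of age bands at baseline, 22-26% at midline (both by completed months) and 45-58% at endline. At endline it also admits about 7 of 18 bands that were never LNS-eligible. The loss falls entirely on the oldest children, so it is not random in age.

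The shares rest on uniform ages, which the protocol does not state, and on how the cohort is defined. They describe what happens if the text is followed as written; nothing in the document shows that it would be. The correction is worth making because the rule governs who is measured and the change costs almost nothing.

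**What to change.** Under Household Surveys, replace Table 6 with Table 7 in both places: the definition of the 1,500 households and the listing of children in selected homes. Use the Table 7 windows in the listing form for households and children alike.

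As minor corrections in the Table 7 footnote, call the 6-28-month midline rule an inclusion criterion, and reconcile 3-59 months with the 3-63 months in the table row. Do not explain 3-63 months as the children aged 3-59 months in July 2014, because those children are 7-63 months old in November and the gloss would add a new inconsistency.

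The cost is four wording corrections and a check of the listing form. No extra data or participants are needed.
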